## Abstract

**Introduction:** Septic shock remains amongst the leading causes of childhood mortality. Therapeutic options to support children with septic shock refractory to initial resuscitation with fluids and inotropes are limited. Recently, the combination of intravenous hydrocortisone with high dose ascorbic acid and thiamine (HAT therapy), postulated to reduce sepsis-related organ dysfunction, has been proposed as a safe approach with potential for mortality benefit, but randomized trials in paediatric patients are lacking. We hypothesize that protocolised early use of HAT therapy (“metabolic resuscitation”) in children with septic shock is feasible and will lead to earlier resolution of organ dysfunction. Here, we describe the protocol of the Resuscitation in Paediatric Sepsis Using Metabolic Resuscitation–A Randomized Controlled Pilot Study in the Paediatric Intensive Care Unit (RESPOND PICU).

**Methods and Analysis:** The RESPOND PICU study is an open label randomized-controlled, two-sided multicentre pilot study conducted in paediatric intensive care units (PICUs) in Australia and New Zealand. Sixty children aged between 28 days and 18 years treated with inotropes for presumed septic shock will be randomized in a 1:1 ratio to either metabolic resuscitation (1 mg/kg hydrocortisone q6h, 30 mg/kg ascorbic acid q6h, 4 mg/kg thiamine q12h) or standard septic shock management. Main outcomes include feasibility of the study protocol and survival free of organ dysfunction censored at 28 days. The study cohort will be followed up at 28-days and 6-months post enrolment to assess neurodevelopment, quality of life and functional status. Biobanking will allow ancillary studies on sepsis biomarkers.

**Ethics and Dissemination:** The study received ethical clearance from Children's Health Queensland Human Research Ethics Committee (HREC/18/QCHQ/49168) and commenced enrolment on June 12th, 2019. The primary study findings will be submitted for publication in a peer-reviewed journal.

**Trial Registration:** Australian and New Zealand Clinical Trials Registry (ACTRN12619000829112). **Protocol Version**: V1.8 22/7/20.

## Introduction

Sepsis, defined as dysregulated host response to infection leading to life-threatening organ dysfunction, ranks amongst the leading causes of childhood mortality (1–3). Sepsis remains responsible for an estimated three million childhood deaths each year worldwide (4, 5). Despite advances in paediatric intensive care practices, the mortality due to septic shock remains high (around 17%) (6–8). Paediatric sepsis survivors often suffer from long-term sequelae, resulting in a lifelong burden to patients, families, and the society (9, 10).

Paediatric septic shock often is a fulminant disease, and affected children deteriorate rapidly (11). Hence, in order to optimize outcomes and prevent irreversible multi-organ damage, future interventions will need to be applied early after presentation. Therapeutic options for children where septic shock persists despite initial resuscitation remain scarce. Current recommendations for treatment of refractory paediatric septic shock include consideration for intravenous hydrocortisone (12). Several large randomized-controlled trials in septic adults have demonstrated earlier reversal of septic shock using treatment with hydrocortisone (13–15). In children, guidelines explicitly state that clinical trial evidence for the role of hydrocortisone in paediatric septic shock remains unclear, however the use of hydrocortisone appears to be very common (16–18). More recently, ascorbic acid (Vitamin C), has been proposed as a sepsis adjunct therapy. Ascorbic acid carries powerful antioxidant properties and *in-vitro* and animal model evidence indicates protective effects on endotoxin-related endothelial damage and organ function (19, 20). Given that thiamine deficiency is associated with high lactate (21) and an increased risk of death (21), a protocol combining hydrocortisone, ascorbic acid, and thiamine (HAT therapy, or so called metabolic resuscitation) has been trialled in adult studies with some reporting mortality benefit (22, 23), while other trials did not observe differences in patient-centred outcomes (24–28). Both thiamine and ascorbic acid carry an excellent safety profile (29). A recent systematic review on metabolic resuscitation (30) identified nine registered RCTs on metabolic resuscitation in adult septic shock, but none in children. Children may be more prone to vitamin C deficiency during sepsis due to comorbidities, malnutrition, a higher metabolic rate, and a higher proportion of patients with a rapidly progressive disease course. A propensity-matched cohort study from the USA reported excellent safety and feasibility of metabolic resuscitation in children with septic shock (31). Adjusted analyses showed decreased 30- and 90-day mortality (*p* < 0.05) in the intervention group compared to hydrocortisone alone and compared to standard care without hydrocortisone.

We therefore designed the pragmatic Resuscitation in Paediatric Sepsis Using Metabolic Resuscitation–A Randomized Controlled Pilot Study in the Paediatric Intensive Care Unit (RESPOND PICU) to test the feasibility of a paediatric RCT comparing metabolic resuscitation vs. standard septic shock management in children aged ≥28 days to <18 years requiring inotropes for suspected septic shock. We hypothesize that a protocol on metabolic resuscitation in children is feasible and that the intervention will lead to faster resolution of shock compared to standard shock management. In this paper, we describe the RESPOND PICU study protocol including the statistical analysis plan.

## Methods

### Study Design and Setting

The RESPOND PICU study is an open label, multicentre, pragmatic randomized controlled pilot trial (RCT) for children aged between 28 days and 18 years who are admitted to PICUs requiring inotrope therapy for presumed septic shock (Figure 1). The study will recruit patients in tertiary PICUs of participating sites in Australia and New Zealand. The trial compares ***metabolic resuscitation*, **defined as hydrocortisone, high dose ascorbic acid, and thiamine, with ***standard care***defined as septic shock management according to institutional protocols (12, 32). The study protocol has been approved by the Children's Health Queensland Hospital and Health Service Human Research Ethics Committee (HREC/18/QCHQ/49168) and is registered with the Australian New Zealand Clinical Trials Registry (ACTRN12619000829112).

**Figure 1 F1:**
[figure not shown]
Draft CONSORT participant flow diagram for RESPOND PICU.

### Participants

#### Inclusion Criteria

Children aged between 28 days and 18 years admitted to PICU and receiving inotrope therapy for septic shock for at least 2 h are eligible (Table 1). Inotropes (and vasopressors) include adrenaline, noradrenaline, vasopressin, milrinone, dopamine, and dobutamine. Patients treated with inotropes, independent on the dose or route of administration are eligible. Children not meeting age criteria, those with chronic liver failure, cardiomyopathy, those with conditions affecting steroid or vitamin metabolism, and children under active chemotherapy will be excluded. In addition, children with palliative care orders, and children who suffered a cardiorespiratory arrest in the 2 h preceding enrolment are excluded.

**Table 1 T1:** Inclusion and Exclusion criteria.

**Rule**	**Criterium**	**Definition**
Inclusion	Age	• Aged ≥28 days and <18 years
	Illness	• Admitted to PICU and treated for septic shock
	Treatment	• Received inotropes for at least 2 h
	Consent	• Parental/caregiver consent prior to or after enrolment
Exclusion	Age	• Preterm babies born <34 weeks gestation that have a corrected age of <28 days
	Treatment	• Received inotropes for >24 h pre-enrolment • Patient is receiving treatment for systemic fungal infection or has documented strongyloides infection at the time of randomization • Patient undergoing active chemotherapy for cancer treatment
	Co-morbidities	• Cardiomyopathy (not due to sepsis) or chronic cardiac failure • Chronic hypertension due to cardiovascular or renal disease, requiring regular antihypertensive treatment. • Known chronic renal failure (defined as requiring Renal Replacement Therapy) • Known chronic hepatic failure (defined as pediatric Sequential Organ Failure Assessment hepatic subscore >0) • Known diseases affecting the steroid axis, including pituitary disease, congenital adrenal hypoplasia, Cushing or Addison's disease • Known glucose-6 phosphate dehydrogenase (G-6PD) deficiency • Patients with known history of oxalate nephropathy • Patients with acute beri-beri disease • Patients with acute Wernike's encephalopathy • Patients with known malaria • Patients with known of suspected scurvy • Palliative care patient/patient with limitation of treatment (not for inotropes, cardiopulmonary resuscitation, extracorporeal membrane oxygenation, intubation or ventilation)
	Illness severity	• Cardiopulmonary arrest in the past 2 h requiring cardiopulmonary resuscitation of >2 min duration, or death is deemed to be imminent or inevitable during this admission. • Major bleeding with haemorrhagic shock • Sepsis is not likely to be the cause of shock
	Previous study enrolment	Enrolment in RESPOND study <6 months prior

The pragmatic protocol stipulates the use of inotropes as the main feature of shock and does not mandate specific vital signs or laboratory thresholds to qualify for shock.

#### Recruitment

Screening and recruitment of participants will occur in the PICU (Figure 1). Study staff will approach the parents or guardians for prospective consent where feasible. Consent will include permission to conduct a follow-up assessment by questionnaire at 6 months post randomization (Figure 2). Separate consent will be sought to allow biobanking for ancillary studies on sepsis biomarkers. If timely informed consent is not feasible (for example if parents are not present immediately or if they are too distressed) the study team can employ consent to continue (33), until parents can be approached to seek written consent. Parents have the option to withdraw consent, which will lead to their child's study data being excluded.

**Figure 2 F2:**
[figure not shown]
Study procedures. ASQ, ages and stages; BRIEF, paediatric Behavior Rating Inventory of Executive Function; FSS, functional status score; LOS, length of stay; MODS, multiple organ dysfunction syndrome; PICU, paediatric intensive care unit; POPC, Paediatric Overall Performance Category; QoL, quality of life.

### Randomization and Blinding

Allocation occurs in a 1:1 ratio to the treatment group (receiving metabolic resuscitation vs. standard shock management). We will use a permuted block randomization with variable block sizes of two, four and six stratified by site. Sealed opaque envelopes will be provided using a randomization sequence generated by The University of Queensland, Brisbane, Australia. Once a child meets eligibility criteria, study staff or treating clinicians are advised to open the next sequential sealed envelope to reveal the allocation of the patient.

Due to the challenges in blinding three drugs, and considering the main aim of this study to investigate feasibility of metabolic resuscitation, the study will be open label.

### Study Interventions

The study treatment should be started immediately after randomization. The RCT compares ***metabolic resuscitation***with ***standard care***.

#### Metabolic Resuscitation

After initial shock treatment including fluids and intravenous inotrope(s), patients then receive additional treatment with hydrocortisone, ascorbic acid, and thiamine:

#### Ascorbic Acid (Vitamin C)

The dosing schedule is 30 mg/kg/dose (maximum 1,500 mg per dose) intravenously every 6 h for the duration of study treatment and will be infused over 30–60 min.

#### Thiamine (Vitamin B1)

The dosing schedule is 4 mg/kg/dose (maximum 200 mg per dose) intravenously every 12 h for the duration of study treatment and will be infused over 30–60 min.

#### Hydrocortisone

The dosing schedule is 1 mg/kg/dose (maximum 50 mg per dose) intravenously every 6 h for the duration of study treatment given as a slow bolus.

Study drugs will be given through an existing peripheral or central intravenous line. Drug delivery will occur through dose error reduction software for infusion devices to ensure safe delivery of applied standardized drug concentrations. The dosing is aligned with the ADRENAL steroid treatment regimen (13), and with the protocol for the VITAMIN trial (24) and has been shown to restore serum ascorbic acid concentrations in critically ill patients (34). The study treatment will be given for a maximum of 7 days, until resolution of shock (defined as cessation of inotropes for at least 4 h), discharge from PICU, death, or if major adverse events related to the intervention manifest, whichever occurs first.

#### Standard Care

Patients in the standard treatment arm can receive hydrocortisone only if clinically indicated at the discretion of the attending ICU staff specialist and should be treated as per the standard institutional approach to septic shock management (12, 32).

#### Other PICU Care

The study protocol does not prescribe what type, dose, or combination of inotropes should be used. Fluid boluses in all three arms can be balanced or unbalanced crystalloid or colloid fluids. Other care including respiratory management, antimicrobials, glucose and electrolyte control, transfusion, sedation, and extracorporeal life support should be provided at the discretion of the treating physician according to local practice.

### Study Outcomes

In addition to feasibility outcomes, the study will assess clinical outcome measures, and proxy measures of intervention efficacy (Table 2). *Feasibility outcomes* include consent rates, time to intervention, hydrocortisone administration prior to randomization, and post randomization in the control group, and protocol violations. Survival free of organ dysfunction censored at 28 days is defined as the *primary clinical outcome*. The pediatric Sequential Organ Failure Assessment (pSOFA) score will be used to assess presence and degree of organ dysfunction (36). All-cause deaths occurring within 28 days of enrolment will be allocated zero organ dysfunction free days. pSOFA scores will be assessed every day during which a patient is admitted in PICU. In children not requiring ongoing respiratory or renal support post discharge from PICU, and not under palliative care, those discharged from PICU will be assumed to have no organ dysfunction which is aligned with the practice at the participating institutions. PICU free survival, survival free of inotrope support, survival free of multi-organ dysfunction, survival free of acute kidney injury (AKI) (37), mortality, PICU and hospital length of stay represent the *secondary clinical outcome measures*. In addition, study nurses will contact families at 28 days to perform a Pediatric Overall Performance Category (POPC) (38) and Functional Status Score (FSS) assessment (39). As a modification from the POPC “good” category (healthy, alert, and capable of normal age-appropriate activities of daily life; medical and physical problems do not interfere with normal activity), we divided the first POPC category into “good/normal” (no medical conditions), and b) “functionally normal” (requires medication and medical input, normal intellectually and physically, able to do activities without restriction).

**Table 2 T2:** Outcomes assessed.

**Outcome**	**Criterium**	**Definition**
Feasibility of the protocol	Recruitment and compliance with study protocol	• Recruitment rates; including (i) proportion of eligible randomized, and (ii) proportion of eligible consented using prospective consent and consent to continue. • Time to initiation of metabolic resuscitation in the intervention arm • Proportion of patients in each study arm which receive hydrocortisone prior to enrolment • Proportion of patients in the control arm which receive hydrocortisone after enrolment • Protocol violations
Primary clinical outcome	Survival free of organ dysfunction	• Organ dysfunction defined as pediatric Sequential Organ Failure Assessment (pSOFA) score >0, and will be assessed daily until day 28 while patients are admitted to PICU. Patients dying within 28 days of presentation will be allocated zero days to correct for the competing effect of mortality on duration of organ dysfunction. Patients discharged alive from PICU to the ward or home not requiring ongoing organ support, and not being palliative, will be assumed to have zero organ dysfunction after PICU discharge.
Secondary clinical outcomes	Patient-centred outcomes	• Survival free of inotrope support at 7 days • Survival free of multiorgan dysfunction at 7 days
		• 28-day mortality • Survival free of PICU censored at 28 days • Survival free of AKI censored at 28 days^*^ • PICU length of stay • Hospital length of stay • Functional Status Score and modified Pediatric Overall Performance Category at 28 days • Neurodevelopment, Quality of Life and Functional status 6 months post enrolment
	Proxy measures of intervention efficacy	• Proportion with serum lactate <2 mmol/l at 6, 12, and 24 h post enrolment • Time to normalization of tachycardia during the first 24 h post enrolment^**^ • Time to shock reversal, defined as cessation of inotropes for at least 4 h censored at 28 days

* *Acute Kidney Injury (AKI) will be assessed using serum creatinine levels to classify according to Kidney Disease: Improving Global Outcomes (KDIGO) criteria. Because no baseline creatinine values were available, we applied the age-specific thresholds used in PELOD-2 to define the presumed baseline creatinine values. KDIGO Stage 1 was defined as an increase in creatinine to 1.5 to 1.9 times the presumed baseline; Stage 2 as an increase 2.0 to 2.9 times; and KDIGO 3 as an increase ≥3.0 baseline and/or the use of renal replacement therapy*.

** *Goldstein et al. (35)*.

Long-term follow-up at 6 months post randomization through questionnaire by proxy on validated domains across quality of life (40) and functional status will be investigated and reported separately from the main analyses.

Furthermore, we will determine *proxy measures of intervention efficacy* such as shock reversal, normalization of lactate, and time to reversal of tachycardia [defined by age-specific thresholds for Systemic Inflammatory Response Syndrome (35)].

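### The primary clinical outcome sets organ dysfunction to zero at PICU discharge whatever the last pSOFA was, so for some survivors it records open-label discharge timing and not organ recovery

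*Protocol article*

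**What the plan says.** The primary clinical outcome is survival free of organ dysfunction up to day 28. Table 2 of the protocol article sets the in-PICU threshold: "Organ dysfunction defined as pediatric Sequential Organ Failure Assessment (pSOFA) score >0", scored daily while the child is in PICU. Under Data Collection, the score components are gathered only until PICU discharge. Deaths within 28 days score zero free days.

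For the time after PICU, Table 2 names a group of children who "will be assumed to have zero organ dysfunction after PICU discharge". It describes that group as "Patients discharged alive from PICU to the ward or home not requiring ongoing organ support, and not being palliative". The text of Study Outcomes words the exemption differently, "In children not requiring ongoing respiratory or renal support post discharge from PICU, and not under palliative care", and gives the reason: "those discharged from PICU will be assumed to have no organ dysfunction which is aligned with the practice at the participating institutions". Neither place requires the last pSOFA to be 0.

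Under Randomization and Blinding, "the study will be open label". Under Other PICU Care, care not fixed by the protocol is left to the treating physician and local practice. The article states no criteria for PICU discharge. The only sensitivity analysis described under Analysis divides the standard-care arm by hydrocortisone use.

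**The concern.** One outcome uses two thresholds. Inside PICU a single pSOFA point is dysfunction; outside it, only continuing support or palliative status counts. A child without support whose score is 1 or 2 has a dysfunction day in PICU and a free day on the ward with unchanged values. The stated reason, institutional practice, may support the view that discharged children need no support, but it does not establish that their pSOFA is 0. Because scoring stops at the PICU door, the trial's own pSOFA data cannot test the assumption afterwards.

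Staff who know the allocation decide when a child leaves. If they discharge one arm sooner for reasons other than organ recovery, that arm gains free days. The abstract hypothesises earlier resolution of organ dysfunction, and the Sample Size section intends the pilot's effect estimates to inform the power of a full trial, so a distortion here would carry forward.

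**Working it through.** **The plan's own figures.** The article gives no effect size, standard deviation or discharge-day figure for this outcome, so there is none to reproduce. Its only sample-size figure, the one-sided lower 95% limit of 66% for 60 of 80 enrolled, concerns recruitment. It reproduces (Wilson 66.3%, Clopper-Pearson 65.8%) and is not in dispute.

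**The scoring rule as a formula.** Take a child alive at day 28 who leaves PICU unsupported, is not palliative and is not readmitted. Let D be the day of PICU discharge and R the day pSOFA reaches 0 and stays there, both counted from enrolment and at most 28.

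- Days scored as dysfunction = min(D, R)
- Scored free days = 28 − min(D, R)
- Free days by actual recovery = 28 − R

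If D ≥ R, the two agree and discharge timing has no effect. If D < R, the score is 28 − D and R drops out.

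**Numbers put in (D and R assumed).**

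| R | D | Scored: 28 − min(D, R) | By recovery: 28 − R |
|---|---|---|---|
| 8 | 4 | 24 | 20 |
| 8 | 5 | 23 | 20 |
| 8 | 6 | 22 | 20 |
| 8 | 8 | 20 | 20 |
| 10 | 4 | 24 | 18 |

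While pSOFA is above 0, each earlier day of discharge adds exactly one free day.

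**Effect on the comparison of arms.** Analysis plans quantile regression for continuous outcomes, so the median is the natural scale, and the shift depends on how many children have D < R. An illustrative simulation gave both arms the same disease course, with 400,000 children per scenario. All distributions are assumptions:

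- 17% die and score 0 (the Introduction puts septic shock mortality at around 17%).
- The last day of support is a gamma variable (shape 2, scale 2), rounded up, plus 1.
- pSOFA reaches 0 a Poisson number of days after support ends, with mean 1 or 3.
- Usual discharge is a Poisson number of days (mean 2) after support ends.
- In one arm discharge is up to 1 or 2 days earlier, but never before support ends.

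| Mean days from end of support to pSOFA 0 | Earlier by up to | Share leaving with pSOFA above 0: usual / earlier | False shift in mean | False shift in median |
|---|---|---|---|---|
| 1 | 1 day | 18% / 35% | 0.19 | 0 |
| 1 | 2 days | 18% / 48% | 0.41 | 0 |
| 3 | 1 day | 58% / 75% | 0.55 | 0 |
| 3 | 2 days | 58% / 85% | 0.95 | 1 |

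The difference by actual recovery was between −0.03 and 0.04 days throughout, which is simulation noise. The mean shifts show the mechanism but are not the planned estimate. The median moves in whole days: not at all in three scenarios and by one day in the fourth.

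**The case against.** The rule is disclosed, limited to children without support or palliative status, and given a reason. Daily scoring ends at PICU discharge, so some post-discharge convention is unavoidable. The share of survivors leaving with pSOFA above 0 is unknown, and nothing in the article shows that knowledge of the arm would move discharge. This is a 60-child pilot whose main aim is feasibility. All of this stands, and it limits the point to a possible distortion. It does not close the gap, since the stated reason does not make the last score 0 and no described analysis looks at the assumption.

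Three stronger readings are tempting, and the documents do not support them.

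- A reader might infer that the primary outcome largely repeats the secondary outcome of PICU-free survival. That holds only if most survivors leave with pSOFA above 0. If a quarter do, the other three quarters are scored on recovery observed in PICU.
- A reader might infer that the result could not be read as faster resolution at all. The Introduction frames the hypothesis as faster resolution of shock. Time to shock reversal, 7-day survival free of inotropes and early lactate do not use the post-discharge rule, and pSOFA is to be graphed over time by arm.
- A reader might take the days lost when dysfunction is counted on through the ward stay as the size of the bias. That change lowers scores in both arms and is not in itself a difference between them.

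**Conclusion.** The point holds in limited form. For 28-day survivors who leave PICU unsupported, not palliative and with pSOFA still above 0, the score is set by the discharge day. In an open-label trial a difference in discharge timing could then pass for a difference in organ recovery. For such a child the size is exact, one free day per day of earlier discharge. For the planned comparison it is unknown: zero or up to about one day in the median under the distributions assumed above. It rests on two quantities that the article does not give, the share of such children and any difference between arms in discharge timing. The matter deserves correction because the estimates are meant to inform a full trial, but it does not undermine the feasibility aim.

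Separately, the exemption is worded as respiratory or renal support in the text and as organ support in general in Table 2. A child leaving PICU on some other organ support would be scored differently under the two.

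**What to change.** 1. From the daily pSOFA already collected, report by arm the number of survivors whose last PICU pSOFA was above 0.
2. Add a sensitivity analysis of the primary clinical outcome, with the same quantile regression, in which those children are not credited with free days from PICU discharge. For example, carry dysfunction forward to hospital discharge or to day 28, and label the result as a bound. Carrying to day 28 gives the lowest score a child could have; carrying to hospital discharge does so only if recovery is complete by then. Either bounds a child's score, not the difference between arms.
3. If the two analyses differ materially, interpret the primary result as faster resolution of organ dysfunction only with caution.
4. Reconcile the wording of ongoing support between the Study Outcomes text and Table 2.

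The cost is one extra analysis and one table row. Hospital length of stay is already an outcome, so no new data are needed. The drawback is that the bound also depends on an unblinded discharge decision, so it shows how far the result leans on the assumption and does not replace the primary analysis.

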### Adverse Events (AEs)

Based on the anticipated severity of the study population informed by recent observational studies in Australian and New Zealand PICUs (7, 11, 41) a proportion of study patients are expected to suffer from complications related to septic shock unrelated to study interventions (42). Major AEs including death, cardiopulmonary arrest, ECMO and amputations will be captured in all patients. In addition, we will report any AE potentially causally related to the study intervention or which is of concern in the investigator's judgement. Specific additional AEs captured include limb ischemia, extravasation injury, hypertension, arrhythmia other than sinus bradycardia or tachycardia, hyperglycaemia, abdominal compartment syndrome, pulmonary edema and confirmed hospital-acquired infection. Adverse events will be assessed routinely until day 28, or until the time of patient discharge from hospital, whichever occurs earlier. The *Data and Safety Monitoring Board (DSMB)* consists of a statistician, an ICU specialist and an emergency specialist will receive regular DSMB reports and immediate access to any serious adverse event reports. The DSMB, once set up, will meet mid-trial and at the completion of the trial.

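### Shock reversal is defined only by inotropes being off for 4 hours, so a child supported by ECMO can be counted as reversed

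*Protocol article*

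**What the plan says.** All references are to the protocol article.

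- **Outcome.** Under Study Outcomes, Table 2 lists among the efficacy proxies: "Time to shock reversal, defined as cessation of inotropes for at least 4 h censored at 28 days".
- **What counts as an inotrope.** The Inclusion Criteria section states: "Inotropes (and vasopressors) include adrenaline, noradrenaline, vasopressin, milrinone, dopamine, and dobutamine". All six are drugs.
- **ECMO as care.** Other PICU Care says that "extracorporeal life support should be provided at the discretion of the treating physician according to local practice".
- **ECMO as harm.** The Adverse Events section says: "Major AEs including death, cardiopulmonary arrest, ECMO and amputations will be captured in all patients".
- **The same wording elsewhere.** The last paragraph under Hydrocortisone gives study treatment for at most 7 days, "until resolution of shock (defined as cessation of inotropes for at least 4 h), discharge from PICU, death", or until a major related adverse event.

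Nothing in the article treats ECMO as continuing shock, as failure, or as a competing or censoring event for this outcome.

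**The concern.** The definition uses drug cessation as a stand-in for recovery of the circulation. That stand-in fails when a machine takes over the circulation and the drugs are stopped for that reason. The child is then recorded both as having a major adverse event and as an efficacy success. Nor does the wording say that the child must be alive.

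The Introduction hypothesises that shock will resolve sooner with the intervention, and among the listed outcomes this one measures that most directly. The trial is open label and ECMO is at the physician's discretion, so ECMO use could differ between arms. The Sample Size section also says that the pilot's estimates will inform the power of a full trial, so a weak definition could be carried forward.

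**Working it through.** **Reading the definition.** The article gives no figure for this outcome (no expected reversal time, no ECMO rate), so there is none to reproduce. The first check is by logic.

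1. Reversal requires only that inotropes have been off for at least 4 hours (Table 2).
2. "Inotropes" means the six listed drugs (Inclusion Criteria). A child on any of these, vasopressors included, has not reversed.
3. ECMO is not on the list, and no other text adds it to the outcome.
4. ECMO is expected to be possible in this cohort. It is left to local practice and recorded as a major adverse event, and Table 1 excludes children with a treatment limitation that rules it out.
5. Hence a child on ECMO with the listed drugs off for 4 hours satisfies the definition.

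**Comparison with neighbouring outcomes.** The article guards against the same problem elsewhere in Table 2. Renal replacement therapy counts as KDIGO stage 3, so a creatinine lowered by a machine is not read as renal recovery. In the primary clinical outcome, deaths receive zero free days. Shock reversal has neither safeguard.

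**Size per child.** With 60 children randomised 1:1, an arm has about 30.

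- 1 affected child: 1/30 = 3.3 percentage points of the arm
- 2 affected: 2/30 = 6.7 points
- 3 affected: 3/30 = 10.0 points

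**Illustration on the median.** The Analysis section names quantile regression for continuous outcomes, so the median is a natural summary. All inputs here are assumptions: an arm of 30; reversal times at exponential quantiles with a 48 h median; 1, 2 or 3 of the slowest children recoded as reversed at 24 h because inotropes stopped on ECMO; all of them in one arm.

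Ordered times: t(i) = −ln(1 − (i − 0.5)/30) × 48/ln 2. This gives t(12) = 33.5, t(13) = 37.3, t(14) = 41.4, t(15) = 45.7 and t(16) = 50.3 h.

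| Children recoded to 24 h | Median is the mean of | Median (h) |
|---|---|---|
| 0 | t(15), t(16) | 48.0 |
| 1 | t(14), t(15) | 43.6 |
| 2 | t(13), t(14) | 39.4 |
| 3 | t(12), t(13) | 35.4 |

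If these children are instead coded as not reversed by day 28, the median stays at 48.0 h. It also stays there if inotropes stop on ECMO later than t(16) = 50.3 h, because the recoded child remains above the median. The shift therefore depends on early cannulation and early drug cessation.

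**The case against.** The strongest reply is that Table 2 is a one-line entry in a condensed article, and that conventions for ECMO could sit in the full protocol or analysis plan. That would answer an omission. Here the article states a definition and a list of qualifying drugs, and together they classify the ECMO case, wrongly for the purpose.

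A second reply is that the consequence is small: shock reversal is one of three proxies in a 60-child pilot, the Abstract frames the hypothesis around organ dysfunction (which the primary clinical outcome measures), and ECMO is reported separately, so an imbalance would be visible. This stands and limits the priority.

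Several stronger readings are tempting, and the article does not support them.

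- **Reversal is declared whatever other circulatory support is running.** Not for drugs: the listed vasopressors are already covered. Only mechanical support is left out.
- **Such a child counts as an early success.** The definition permits an early event but does not force one.
- **Reversal is fixed at the first 4-hour gap even if inotropes restart.** The text does not say which gap counts and is silent on restarts.
- **The treatment-duration rule and the adverse event list contradict each other.** They do not. One ends study treatment and the other lists events to record.
- **"Survival free of inotrope support at 7 days" is equally wrong.** It measures what its name says. Counting ECMO days against it would make it a different outcome, which is a preference and not a correction.

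**Conclusion.** The point holds in a limited form. The stated definition lets a child on ECMO, with the listed drugs off for 4 hours, count as shock reversed, and it does not require survival. This is a misclassifying rule for one efficacy proxy.

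Its effect cannot be sized from the article. It depends on how many children are cannulated, how many of those then stop every listed drug for 4 hours, and when. Each such child is 3.3 percentage points of a 30-child arm, and the number may be very small or zero. The median shifts shown above rest wholly on assumed inputs. A bias between arms further requires unequal ECMO use, for which the article gives no evidence. The feasibility outcomes and the definition of the primary clinical outcome are not touched. Priority is low to moderate; the case for acting is mainly that the change is cheap.

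**What to change.** In Table 2, for the outcome only, define shock reversal as: alive, off all listed inotropes and vasopressors for at least 4 hours, and not on ECMO or other mechanical circulatory support; a child who dies before meeting this is treated as not reversed. Report, per arm, the number of children whose classification changes from the present wording.

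The last paragraph under Hydrocortisone uses the present wording to end study treatment. The trial team should state whether the outcome definition and the treatment-ending definition are meant to stay the same. No clinical rule is proposed here.

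Cost: a wording change and one extra line of reporting. ECMO is already recorded in all patients and organ support daily until PICU discharge (Data Collection), which is enough to identify the affected children. The downsides are slightly longer reversal times and an outcome definition that would differ from the treatment-ending wording unless the team aligns them.
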